#### 2.4.5. Follow-up visits.

(1) Interim Visit (Week 4 ± 3 days, outpatient): Includes clinical evaluation, laboratory tests (metabolic, β-cell function, immune markers), CGM data collection (Weeks 2–4), PROs, and AEs/Serious adverse events (SAEs) documentation.(2) Final Visit (Week 12 ± 3 days, outpatient): A comprehensive reassessment, including all parameters from the interim visit plus final gut microbiome and safety laboratory samples. CGM data from Weeks 10–12 are collected. The study concludes with database lock and unblinding.

A detailed schedule is provided in Table 2.

**Table 2 pone.0343078.t002:** Study visit schedule.

Process	Screening period	Run-in period 1	Baseline period	Run-in period 2	Intervention period	Mid-term follow-up	Final follow-up
	Day −17	Day −17 to Day −3	Day −3	Day −3 to Day 0	Day 0 to Day 6	Week 4 ± 3 days	Week 12 ± 3 days
Obtain informed consent	**√**						
Basic characteristics	**√**						
Lifestyle survey			**√**				
Record anthropometric measurements			**√**			**√**	**√**
Average total daily insulin dose (Past 1–2 Weeks)			**√**			**√**	**√**
Glucose + C-peptide (Fasting and MMT 2h)			**√**			**√**	**√**
HbA1c	**√**		**√**			**√**	**√**
Islet autoantibody titer			**√**			**√**	**√**
Treg/Th17 ratio			**√**			**√**	**√**
Lipids profile			**√**			**√**	**√**
Liver function			**√**				**√**
Renal function			**√**				**√**
Thyroid function			**√**				**√**
Infection markers and inflammatory cytokines			**√**			**√**	**√**
Intestinal Barrier-Related Antibodies			**√**			**√**	**√**
Safety assessments			**√**		**√**	**√**	**√**
AEs and SAEs			**√**			**√**	**√**
Gut microbiome			**√**			**√**	**√**
Serum metabolomics			**√**				**√**
Bowel cleansing				**√**			
Oral yFMT capsules					**√**		
Standard insulin therapy		**√**	**√**	**√**	**√**	**√**	**√**
CGM monitoring		**√**			**√**	**√**	**√**
Questionnaires			**√**			**√**	**√**
Feasibility endpoints							**√**
Provision of yFMT to the placebo group after unblinding							**√**

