### 2.5. Endpoints

The primary endpoint is change in the composite achievement rate of TIR > 70% and TBR3.9 < 4% at 3 months (Weeks 10–12) post-intervention compared to baseline (days −17 to −3 during the run-in period). Secondary efficacy endpoints included glycemic metabolism, β-cell function, insulin sensitivity, immunomodulation, Intestinal Barrier-Related Antibodies, inflammatory markers, gut microbiome and metabolites, PROs, lipid profile and TDD. The 1-month (Weeks 2–4) assessment is defined as a secondary endpoint to evaluate early glycemic changes. Feasibility endpoints include: (1) recruitment rate (proportion of screened participants enrolled); (2) retention rate (proportion of participants completing the 12-week follow-up); (3) intervention adherence (percentage of prescribed capsules consumed); and (4) acceptability (participant-reported tolerability and willingness to undergo treatment). Safety endpoints comprised the incidence of AEs (such as gastrointestinal symptoms, infection-related events, immune-related reactions, and allergic responses), as well as the incidence of serious AEs (SAEs, including severe hypoglycemia, diabetic ketoacidosis, hospitalization, disability, life-threatening events, or death). Detailed information is provided in Table 3.

**Table 3 pone.0343078.t003:** Study endpoints.

Primary endpoint	change in the composite achievement rate (TIR > 70% and TBR3.9 < 4%) at 3 months (Weeks 10–12) post-intervention
**Secondary endpoints**	change in the composite achievement rate (TIR > 70% and TBR3.9 < 4%) at 1 month (Weeks 2–4) post-intervention
	Changes in glycemic parameters at Week 4 and Week 12 post-intervention
	Changes in pancreatic β-cell function at Week 4 and Week 12 post-intervention
	Changes in insulin sensitivity indicators at Week 4 and Week 12 post-intervention
	Changes in TDD at Week 4 and Week 12 post-intervention
	Changes in infection and inflammatory markers at Week 4 and Week 12 post-intervention
	Changes in Intestinal Barrier-Related Antibodies at Week 4 and Week 12 post-intervention
	Changes in cellular immune indicators at Week 4 and Week 12 post-intervention
	Changes in lipid profile at Week 4 and Week 12 post-intervention
	Changes in gut microbiota composition and abundance at Week 4 and Week 12 post-intervention
	Changes in serum metabolomic profiles at Week 12 post-intervention
	Changes in PROs at Week 4 and Week 12 post-intervention
**Feasibility endpoints**	Recruitment rate
	Retention rate

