### 2.10. Statistics and analysis

Efficacy analyses will be performed in the intention-to-treat population. For the primary efficacy endpoint, participants with missing primary endpoint assessments will be considered non-responders using a non-responder imputation approach in the intention-to-treat analysis. Safety analyses will be performed in the safety analysis set. Normality of continuous variables will be assessed using the Shapiro-Wilk test at each time point. Normally distributed data will be presented as mean±standard deviation and analyzed using independent samples t-test (between-group) or paired t-test (within-group). Non-normally distributed data will be presented as median (Q1, Q3) and analyzed using Mann-Whitney U test (between-group) or Wilcoxon signed-rank test (within-group). Categorical data will be expressed as count (percentages) and analyzed using Fisher’s exact test.

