For the primary efficacy endpoint assessed from baseline to Week 12 post-intervention, a generalized estimating equation (GEE) model with a binary distribution, logit link function, and an exchangeable correlation structure will be employed. The model includes group, time, and their interaction as fixed effects, with baseline composite achievement status as a covariates, as appropriate. Given the pilot nature of the study (n = 20), Fisher’s exact test will additionally be performed at each time point as a sensitivity analysis to ensure robustness. For continuous secondary outcomes, linear mixed-effects models will be applied with group, time, and their interaction as fixed effects, the baseline value of the respective outcome as a covariate, and age and T1DM duration as additional covariates, with a random intercept for each participant. Multicollinearity will be assessed using the variance inflation factor (VIF), with VIF > 10 indicating significant collinearity. Given the limited sample size, a parsimonious sensitivity model including only baseline value, group, and time will also be performed to assess robustness against overfitting. Feasibility outcomes will be assessed descriptively. All feasibility endpoints will be presented as frequencies and percentages, with 95% confidence intervals where appropriate. For secondary continuous outcomes and covariates, missing data will be addressed using multiple imputation. Twenty imputed datasets will be generated using baseline outcome values, age, T1DM duration, and treatment group as predictors, and results will be pooled using Rubin’s rules. Logistic regression analysis will be used to explore factors associated with response to yFMT treatment. CGM metrics, as recommended by international expert consensus, will be calculated using Glyculator 2.0 software (Medical University of Lodz, Poland). All statistical analyses will be performed using R software (version 4.3.2) and GraphPad Prism 9.0. Statistical significance is defined as two-sided *P* < 0.05. Bonferroni correction will be applied for multiple comparisons in post hoc analyses.

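### Imputing continuous secondary outcomes without the Week 4 value can bias Week 12 differences if drop-out follows Week 4 response, and the sensitivity model without group-by-time estimates only a two-visit average

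*Protocol article*

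**What the plan says.** All the analysis statements are in section 2.10 of the protocol article.

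- **Scope of imputation:** "For secondary continuous outcomes and covariates, missing data will be addressed using multiple imputation".
- **Predictors:** "Twenty imputed datasets will be generated using baseline outcome values, age, T1DM duration, and treatment group as predictors".
- **Main model:** "linear mixed-effects models will be applied with group, time, and their interaction as fixed effects", adjusted for the baseline value, age and diabetes duration, and "with a random intercept for each participant".
- **Sensitivity model:** "a parsimonious sensitivity model including only baseline value, group, and time will also be performed to assess robustness against overfitting".

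The data available are set out elsewhere. Section 2.4.5 schedules an "Interim Visit (Week 4 ± 3 days, outpatient") at which laboratory and CGM data are collected. Table 3 in section 2.5 defines most continuous secondary endpoints at both visits, for example "Changes in glycemic parameters at Week 4 and Week 12 post-intervention". Serum metabolomics is the exception, being measured after baseline only at Week 12. Section 2.9 sets 10 participants per group.

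**The concern.** The mixed model with a random intercept treats a participant's Week 4 and Week 12 values as correlated. The imputation that precedes it does not. A participant who attends Week 4 and then leaves has a Week 12 value drawn as if Week 4 had never been seen. If people leave because of how they stood at Week 4, the imputed values are centred in the wrong place.

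Such drop-out is conceivable under the protocol. Section 2.7 makes a serious adverse event a reason for withdrawal, and section 2.5 counts severe hypoglycemia and ketoacidosis among these events. Section 2.9 wants preliminary effect estimates for planning a pivotal trial, so a systematic shift in an estimate matters even without formal testing.

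The sensitivity model is a separate matter. It is meant to guard against overfitting, but it removes the interaction together with the two covariates. Its group coefficient is then a different quantity from the visit-specific effects named in Table 3.

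**Working it through.** The plan gives no figure for drop-out, correlations or effects, so there is none to reproduce. Assumptions: outcome SD 1; correlation 0.5 between baseline and each later visit; correlation 0.7 between Weeks 4 and 12; Week 4 complete; 10% or 20% missing at Week 12.

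**Step 1: why bias can arise.** Without Week 4 as a predictor, leavers are treated like stayers with the same baseline and arm. In arm a, the imputed Week 12 mean is then off by about

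Δₐ = pₐ × β × (mean Week 4 of stayers − mean Week 4 of leavers, given baseline),

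where pₐ is the fraction missing and β the slope of Week 12 on Week 4 given baseline. Ignoring age and duration, β = (0.7 − 0.5 × 0.5) / (1 − 0.5²) = 0.45 / 0.75 = 0.6. The bias in the group difference is Δ(active) − Δ(placebo). It vanishes if drop-out is unrelated to Week 4 given baseline, or if the two arms' shifts are equal.

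**Step 2: size, by simulation with very large samples** (Week 12 difference by ANCOVA on imputed data, SD units).

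| Drop-out mechanism | Bias, predictors as listed | Bias, Week 4 added |
|---|---|---|
| Random, or baseline only | within 0.011 of 0 | about 0 |
| Week 4, same in both arms, no effect | about 0 | about 0 |
| Week 4, same in both arms, effects 0.5 and 0.5 | −0.03 to −0.05 | about 0 |
| Week 4, same in both arms, effects 0.8 and 0.4 | −0.06 to −0.09 | about 0 |
| Week 4, active arm only | +0.09 to +0.16 | about 0 |
| Week 4, opposite directions by arm | +0.13 to +0.25 | about 0 |

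Rows three and four are not zero because a treatment effect at Week 4 makes a shared rule remove unequal fractions: 25% against 15%, and 28% against 12%, at 20% missing overall.

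The formula shows how strong the last row's mechanism is. A bias of 0.25 with 20% missing per arm implies a stayer–leaver gap of 0.25 / (0.6 × (0.2 + 0.2)) = 1.04 SD, which is a strong dependence. A weaker one shrinks the bias in proportion.

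**Step 3: at 10 per arm** (20% missing, effects 0.5 and 0.5).

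- Same mechanism in both arms: bias −0.07 as listed, −0.02 with Week 4.
- Opposite mechanisms: bias +0.25 as listed, +0.02 with Week 4.
- Empirical SD of the estimate: 0.49 to 0.52 either way, so adding Week 4 costs no appreciable precision. The largest bias is 0.25 / 0.51 ≈ 0.5 standard errors; the shared-mechanism one is 0.07 / 0.49 ≈ 0.14.

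**Step 4: the same on a TIR scale** (assumed SD 12 points, correlations 0.7, true effect 8). Imputation without Week 4 gives about 7.9 under random drop-out, 7.7 under Week 4-dependent drop-out in both arms, and 6.6 when mainly placebo participants with low Week 4 values leave. With Week 4 the answer is about 8.0. The worst shift is (8 − 6.6) / 12 = 0.12 SD. The SD of the estimate at n = 20 is about 4.5 to 5 points, or 0.38 to 0.42 SD.

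**Step 5: mixed model without imputing outcomes.** Fitted to incomplete Week 4 and Week 12 data (20% missing), its Week 12 bias was −0.005 to −0.023, against −0.08 to +0.23 for the imputation as listed.

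**Step 6: sensitivity model.** With both visits complete and no interaction, the group coefficient is (Week 4 effect + Week 12 effect) / 2.

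| True effects (Week 4, Week 12) | Expected average | Sensitivity model | Week 12 effect, interaction model |
|---|---|---|---|
| 0, 0.8 | 0.40 | 0.43 | 0.83 |
| 0.8, 0.4 | 0.60 | 0.60 | 0.41 |
| 1.0, 0 | 0.50 | 0.52 | 0.01 |
| 0.5, 0.5 | 0.50 | 0.49 | 0.48 |

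The two quantities coincide only when the effects are equal. If baseline were also entered as a time level, the coefficient would fall to about a third of the sum of the effects.

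**The case against.** **A reader might infer that drop-out as such biases the Week 12 effects.** The documents do not support that. Random and baseline-dependent drop-out give no bias. A mechanism shared by both arms gives at most about 0.09 SD, and larger values need one that differs by arm. Nothing in the protocol says that it will: the withdrawal rules apply to both arms, and section 2.4.7 describes measures to limit missing data. Someone lost before Week 4 has no Week 4 value to use, so the point does not reach them.

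**A reader might also infer that disagreement between the main and sensitivity models cannot be interpreted.** That goes too far. With complete imputed data, the no-interaction coefficient equals the average of the two visit effects from the same model with the interaction; four simulated datasets of 20 agreed to five decimals. Averaging the main model's two visit effects and comparing that with the sensitivity coefficient isolates the removal of age and duration. Table 3 does not rank the visits, so an average is a legitimate summary. What remains is that the sensitivity model does not directly check either visit-specific effect.

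**The predictor list does not say that it is exhaustive**, and no algorithm is named, so a fuller analysis plan might bring in the other visit. This lowers certainty, but the article gives a definite list and Week 4 is absent from it.

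**The distribution checks** ("Normality of continuous variables will be assessed using the Shapiro-Wilk test at each time point") and the simple tests chosen from them may look like a competing analysis. Section 2.10 assigns mixed models specifically to continuous secondary outcomes, and the present point does not depend on those tests.

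**Conclusion.** The point holds as a low-severity improvement to the secondary analyses. As listed, the imputation predictors discard the Week 4 value and do not match the mixed model. The Week 12 bias is conditional on drop-out that follows Week 4 response: zero to about 0.09 SD if the mechanism is shared, and about 0.1 to 0.25 SD if it differs by arm. Against a standard error of roughly 0.4 to 0.5 SD, even the largest value is about half a standard error. These sizes rest on the assumed correlations and 10 to 20% missing, none of which the documents give.

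That the sensitivity model estimates a two-visit average follows from its stated terms and needs no assumption about missing data.

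The imputation point does not touch the primary endpoint, which uses non-responder imputation, or serum metabolomics, which has no Week 4 sample.

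**What to change.** 1. **Imputation.** Either add the other visit's value of the same outcome to the predictors, or fit the mixed model directly to the observed Week 4 and Week 12 values and keep imputation for missing covariates. The second route is simpler and is valid when drop-out depends only on observed data, including Week 4.
2. **Sensitivity model.** Remove age and diabetes duration only, and keep baseline value, group, time and group-by-time. A difference from the main model at either visit then reflects the covariates alone.

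The cost is a change to two sentences in section 2.10 and a few lines of code. No visit, sample or procedure changes.

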**Discussion:**

Our findings will offer new insight into the feasibility and effects of oral yFMT capsules in adults with T1DM and provide the necessary evidence to power a subsequent multicenter large-scale study. Exploratory biomarker analyses conducted within this study may further pave the way for future individualized microbiome‑based therapeutics.

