#### 2.4.3. Randomization and blinding.

Following the completion of the run-in period, eligible participants will be randomized in a 1:1 ratio to either the intervention or the control group. Randomized allocation sequences will be generated using a permuted block design in R software. Sequentially numbered, opaque, sealed envelopes will be prepared and stored by a non-investigational team member. To minimize selection bias, the randomization codes are assigned by an independent researcher. Once an eligible participant is enrolled, the principal investigator notifies the independent researcher to open sequentially the sealed envelope for allocation. yFMT and placebo capsules are identical in appearance, shape, odor, and specifications.

The investigational capsules will be assigned predefined random codes that were dispensed without selection. Randomization number is not allowed to be reassigned following participant discontinuation. The randomization code will be securely maintained by an independent statistician throughout the study. The code will remain inaccessible to investigators, participants, and endpoint assessors, except for authorized access by the independent Data Monitoring Committee (DMC) during the pre-specified interim analysis. Full unblinding will occur only after database lock and completion of the final analysis.

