### 2.9. Sample size and pilot trial rationale

This is a pilot study. The primary objectives are to assess the feasibility (recruitment, adherence) and safety of the oral yFMT, to evaluate the preliminary effciency, and to collect preliminary effect-size estimates for the planning of a subsequent pivotal trial.

As no prior data exist on achieving the composite glycemic target (TIR > 70% with TBR3.9 < 4%) following yFMT in adults with T1DM, a traditional sample size calculation based on an anticipated effect size was not feasible. The sample size for this trial was therefore determined in accordance with methodological best practices for pilot trial design. We referenced the guidance proposed by Wang et al., which indicates that a pilot study for a future definitive trial with 90% power and a two-sided alpha of 0.05 typically requires approximately 10–25 participants per group to provide meaningful parameter estimates for small-to-moderate effect sizes [23]. Based on this, and considering the common requirement for assessing primary feasibility objectives (e.g., recruitment rate, procedural acceptance), a sample size of 10 participants per group was set.

A pre-planned interim analysis will be conducted after the first 10 participants (50% of the total planned sample) have completed the 12-week follow-up. During this interim analysis, the DMC will review unblinded data, including safety outcomes and the primary composite endpoint, to evaluate safety and obtain preliminary treatment effect estimates for future sample size planning. No formal hypothesis testing will be performed, and no sample size re-estimation is planned for the current trial, consistent with its pilot nature. Based on the DMC’s review, the trial may continue as planned, be modified, or be terminated early if unacceptable safety concerns or clear futility are observed.

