However, our study is also limited by a relatively small sample size, single-center design, and relatively short (12-week) follow-up period, which might be insufficient to assess long-term glycemic benefit and sustained impact on residual islet β cell function. Additionally, several recipient-related factors may further complicate the interpretation of outcomes. Longer T1DM duration has been associated with reduced residual β-cell function, potentially limiting the capacity for β-cell preservation [14]. Age may influence both gut microbiota composition and immune responsiveness [24]. Underlying comorbidities are also recognized as important determinants of the efficacy and safety of yFMT [25]. Although age and T1DM duration were adjusted for in the statistical analyses and individuals with relevant comorbidities were excluded per protocol, the limited sample size (n = 20) precludes robust subgroup analyses for these variables, as well as for other potential confounders. This further underscores a key limitation of the present pilot study and highlights the need for future adequately powered trials to systematically evaluate these potential effect modifiers.

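### The planned logistic regression for predictors of yFMT response rests on about 10 treated participants and has no stated small-sample safeguard; a default fit would give unstable or undefined odds ratios

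*Protocol article*

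**What the plan says.** Section 2.10 plans one analysis of predictors: "Logistic regression analysis will be used to explore factors associated with response to yFMT treatment". It says nothing further about that model. The same section sets a general rule, "Statistical significance is defined as two-sided *P* < 0.05", and names R as the main software.

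The size of the treated arm follows from two statements. Section 2.9 says "a sample size of 10 participants per group was set", and section 2.4.3 says "eligible participants will be randomized in a 1:1 ratio to either the intervention or the control group". Section 2.4.6 keeps the later open-label yFMT data from the placebo group apart from the primary analysis.

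Elsewhere in section 2.10 the small sample is taken into account. For the primary endpoint, "Given the pilot nature of the study (n = 20), Fisher’s exact test will additionally be performed at each time point". For the continuous secondary outcomes, a reduced model guards against overfitting. The limitations paragraph of section 3 adds that "the limited sample size (n = 20) precludes robust subgroup analyses for these variables", referring to age, diabetes duration and comorbidities.

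**The concern.** Before unblinding, only the yFMT arm can respond to yFMT, so the natural reading is a logistic model in about 10 people, of whom an unknown number respond. At that size ordinary maximum likelihood often has no finite solution, and where it has one the odds ratio is very imprecise. The article adds small-sample protection to its other two model families and states none for this one, which has the least data.

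There is also a question of interpretation. Participants may adjust insulin on CGM data (section 2.4.4). Entry is by HbA1c or TIR (section 2.3), so some may start with TIR already above 70%. Missing outcomes count as non-response (section 2.10). In a treated-only model, a factor that predicts good control on insulin, or predicts dropout, looks the same as a factor that changes the effect of yFMT.

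At stake is the reliability of any odds ratio reported from this analysis, not the trial's main conclusions.

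**Working it through.** **Inputs from the article.** 10 per group, 1:1 allocation, two-sided 0.05. The stated total reproduces: 2 × 10 = 20, and the interim at 10 participants is 10/20 = 50%. No power or precision figure is given for the regression, so there is none to reproduce.

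**Assumptions.** Section 2.9 says "As no prior data exist on achieving the composite glycemic target", so the response rate is unknown; 20%, 30% and 50% are used. Factors are independent standard normal, with one of them active at an odds ratio (OR) of 1, 3 or 5 per SD. The number of factors is varied from 1 to 4.

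**1. Binary factor, Wald test, by enumeration.** For a 2×2 table with cells a, b, c, d, z = ln(ad/bc) / √(1/a + 1/b + 1/c + 1/d). Over all tables with n = 10 and no empty cell, the most extreme is 4/5 against 1/5:
- OR = (4 × 4)/(1 × 1) = 16, and ln 16 = 2.773
- SE = √(1/4 + 1 + 1 + 1/4) = √2.5 = 1.581
- z = 2.773/1.581 = 1.75, P = 0.080

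No table with a finite odds ratio reaches 0.05. This needs no assumed response rate.

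**2. One continuous factor, Wald test, by simulation.** There were 0 rejections in 3,000 trials at every OR from 1 to 50 per SD, at 30% and at 50% response. By the rule of three the upper 95% bound is 3/3,000 = 0.1%.

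**3. Spread of the estimate with no association.** The central 95% of estimated odds ratios per SD was about 0.03 to 22 in one simulation and 0.03 to 31 in another at 30% response, and 0.07 to 17 at 50%. The tail percentiles vary between runs, hence about 0.03 to 20-30.

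**4. Share of trials with no finite fit** (separation, or all outcomes the same; 1,500 trials per setting):

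| Factors | 30% response, OR 1 / 3 / 5 | 50% response, OR 1 / 3 / 5 |
|---|---|---|
| 1 | 7% / 14% / 21% | 2% / 9% / 18% |
| 2 | 19% / 30% / 41% | 9% / 23% / 32% |
| 3 | 35% / 52% / 60% | 26% / 45% / 53% |
| 4 | 63% / 74% / 79% | 51% / 67% / 75% |

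With 20% response included, the ranges are 2-28% (one factor), 9-47% (two), 26-68% (three) and 51-84% (four).

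The response rate in these runs is set at the average value of the factors. With a strong factor the overall rate is higher. At a nominal 20%, OR 5 and two factors, all outcomes were the same in 3.5% of trials, which implies an overall rate near 1 − 0.035^(1/10) = 28%. If 20% is meant as the overall rate, the upper ends are therefore understated.

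**5. Other tests and sets.** At n = 10, one factor, OR 5 and 30-50% response, the likelihood-ratio test rejects in 52-53% of trials, but its type I error is 9-10%. The exact Mann-Whitney test rejects in 30-33%. With all 20 participants and one factor, Wald power at OR 5 is about 35%, 45% and 55% at 20%, 30% and 50% response, and 1-3% of trials have no finite fit. That model speaks to response to yFMT only if it carries a treatment-by-factor term, which these figures do not include.

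**The case against.** The strongest reply is that the article does not specify the analysis examined here. It names logistic regression and no more. Maximum likelihood, Wald tests, several factors and a treated-only set are all supplied by the reader, and an article may leave such detail to the full plan. A single-factor Firth or exact fit would itself be logistic regression and would satisfy the sentence. This stands, and it makes the point conditional on a default fit.

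Three stronger readings are tempting and are not supported.

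- **That logistic regression cannot be used at all at this size.** One-factor fits usually exist. Zero power is a property of the Wald test; likelihood-ratio and rank tests keep some power. The high failure rates need three or four factors together, which the article does not plan.
- **That the odds ratios will steer patient selection in the next trial.** No section says so. Section 2.9 carries forward feasibility, safety and effect-size estimates. The abstract says "Exploratory biomarker analyses conducted within this study may further pave the way for future individualized" therapeutics, but it does not mention this regression and already uses cautious wording, so it needs no change.
- **That section 3 contradicts section 2.10.** The limitation on subgroup analyses is a caution about interpretation. It sits awkwardly beside a search for response factors in half the sample, but an exploratory analysis can coexist with it.

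The reply does not dispose of the point. The article commits to a method by name, protects its other models against the small sample and leaves this one without stated protection.

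**Conclusion.** The concern holds in a limited form. With about 10 treated participants, a default maximum-likelihood fit with Wald tests would essentially never reach P < 0.05 with one factor, would give odds ratios spanning roughly three orders of magnitude when nothing is there (30/0.03 = 1,000), and would have no finite solution in about 2-28% of trials with one factor and 51-84% with four. Switching to the likelihood-ratio test restores some power but roughly doubles the nominal 5% error rate, to 9-10%. Independently of the test, a treated-only model cannot separate prognosis from modification of the yFMT effect.

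The enumeration for a binary factor depends only on n = 10 and the Wald test. The remaining figures rest on assumed response rates of 20-50%, normal independent factors and odds ratios of 1-5 per SD (up to 50 for the one-factor Wald test). The analysis is exploratory and absent from the endpoints in Table 3, so the consequence is modest and no main conclusion is affected.

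**What to change.** Replace the sentence in section 2.10 with a descriptive display: prespecified candidate factors by responder status (individual values, median and range), shown separately for the yFMT and placebo arms. The placebo table lets a reader see whether a pattern is particular to yFMT.

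If a model is kept, fit one prespecified factor at a time by Firth-penalised or exact logistic regression, state the analysis set, report each estimate with its interval, do not select factors by P value, and label the results hypothesis-generating.

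The cost is wording only; sample size, visits and data collection do not change. The downside is that no conventional multivariable odds ratios or P values for predictors are reported.
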